#### Sample Size Determination

Prerecruitment power calculations were conducted to determine the required sample size for the study. Required statistical power (1-β) was set to 90%, and significance level (α) was set at .05. The study was planned to detect medium intervention main effects (Cohen *d*=0.50) in the primary outcome variables: situational engagement, alertness, and inhibition. Definition of the desired minimum detectable effect size was, as usual, a compromise between academic desire and study costs and supported by published works on the outcomes (eg, alertness [79,80], inhibition [81,82]).

The required sample size *n* for an individually randomized controlled trial would be

$n_{IRCT}=\frac{{\left(Z_{1-\alpha /2}+Z_{1-\beta }\right)}^{2}\cdot 2\sigma^{2}}{\Delta^{2}}$,

where $Z_{x}$ is the *x*th quantile of the standard normal distribution, α is the size of the test (ie, level of significance), β is 1 – required level of statistical power, Δ is the minimum detected difference in the levels of outcome, and $\sigma^{2}$ is the assumed overall variance of the outcome variable.

In educational interventions, participants are most often divided into school classes, and therefore, individual randomization for intervention groups is rarely feasible. This cluster-randomization weakens the design generally, and the required sample size increases by a factor called the design effect.

In our study design, individuals serve as their own controls by visiting the two intervention treatments and a control treatment in randomized order. The design effect gets a form of

$DE_{CRIC}=2\left(1-\rho_{1}-\rho_{2}\right)$,

where $\rho_{1}$ is the assumed intra-subject correlation and $\rho_{2}$ is the assumed intra-cluster correlation.

Assuming the variance structure as observed in the pilot study (Matikkavire), $\rho_{1}=0.31$ and $\rho_{2}=0.01,$ the design effect is $2\left(1-0.31-0.01\right)=1.36$ and the required sample is n=115 individuals to be crossed over the treatments. By assuming 33 students per class and a 70% student participation rate, we need to recruit five classes. To balance the design, we decided to recruit six classes such that two classes would have been randomized to each of the three intervention arms, where the order of treatments is rotated. As the number of volunteering participants per group remained lower than expected, more groups were invited, and eventually, the recruitment continued in a second wave in the autumn of 2024 to obtain the desired statistical power.

The forthcoming subgroup analyses (eg, sex-specific analyses) and moderation analyses (moderating factors will include physiological and psychological state, and physical and academic competence of the student) have less statistical power to detect medium interaction effects. Statistical power is approximated for subgroups by standard methods as discussed above, and for more complex moderation analyses by, eg, post data-collection Monte Carlo simulation. The post hoc power calculations are not used to determine sample size, but to support the confidence of the interpretation of the results of the moderation models.

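### The crossover design effect counts the factor 2 twice: the stated inputs imply about 58 students, not 115, for a within-student difference in outcome levels

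*Protocol article*

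**What the plan says.** All of this is in the protocol article, section Sample Size Determination.

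- **Error rates:** "significance level (α) was set at .05", used through the 1-α/2 quantile and so two-sided. For power, "Required statistical power (1-β) was set to 90" per cent.
- **Target effect:** "The study was planned to detect medium intervention main effects (Cohen *d*=0.50) in the primary outcome variables", which are situational engagement, alertness and inhibition.
- **Base formula:** introduced by "The required sample size *n* for an individually randomized controlled trial would be", it is (Z₁₋α/₂+Z₁₋β)²·2σ²/Δ². Here "Δ is the minimum detected difference in the levels of outcome" and σ² is the overall variance of the outcome.
- **Crossover adjustment:** "In our study design, individuals serve as their own controls by visiting the two intervention treatments and a control treatment in randomized order". For this the article uses a multiplier of 2(1-ρ1-ρ2), with ρ1 the intra-subject and ρ2 the intra-cluster correlation.
- **Result:** with ρ1=0.31 and ρ2=0.01 from a pilot, the design effect is 1.36 and "the required sample is n=115 individuals to be crossed over the treatments".
- **Use:** five classes, then six for balance, are derived from this number. Volunteering fell short, so further groups were approached; the article adds that "eventually, the recruitment continued in a second wave in the autumn of 2024 to obtain the desired statistical power". Subgroup power, it says, will be approximated with the methods that this section has just set out.

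**The concern.** The 2σ² in the base formula is the variance of a difference between two independent measurements, which makes the result a per-arm number. Letting each student supply both measurements shrinks that variance by the factor 1-ρ1-ρ2. It brings in no further factor of 2.

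A check that needs no reference is to set ρ1=ρ2=0. Then n students crossed over two treatments give n independent observations per treatment, exactly as n per arm does in a parallel trial. The multiplier must be 1, but the printed formula gives 2. The doubling cannot be a conversion from per-arm to total either, because the result is labelled as individuals who are crossed over.

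At stake is whether the stated sample size, power and detectable effect belong together. Recruitment relied on the number, and the same formula is due to be reused for subgroup power that has not yet been reported.

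**Working it through.** **Inputs (Sample Size Determination):** two-sided α=.05, power 90%, Δ/σ=0.50, ρ1=0.31, ρ2=0.01. From Study Design and Participants: 168 students in 17 course groups, of whom 74 in 10 groups were in the first wave.

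**1. Reproduce the plan's figure.**
(1.9600+1.2816)² = 10.507.
Base size: 10.507×2/0.25 = 84.06.
Printed design effect: 2(1-0.31-0.01) = 1.36.
84.06×1.36 = 114.3, rounded up to **115**. The multiplication is right.

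**2. Confirm that the base size is per arm.** In a parallel comparison at d=0.50, 85 per arm gives 90.3% power, whereas 85 in total gives 63.5%.

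**3. Within-student difference in levels.** Under the protocol's variance structure, Var(difference) = 2σ²(1-ρ1-ρ2), so
n = 10.507×2×0.68/0.25 = 84.06×0.68 = 57.2, rounded up to **58**.

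**4. Power on the stated inputs.** Power = Φ(0.5/√(2×0.68/n) - 1.96); detectable d at 90% power = 3.2415×√(2×0.68/n).

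| n | Power at d=0.50 | Detectable d (90% power) |
|---|---|---|
| 58 | 90.4% | 0.50 |
| 74 | 95.8% | 0.44 |
| 115 | 99.6% | 0.35 |
| 168 | 99.98% | 0.29 |

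A simulation with subject variance 0.31, cluster variance 0.01 and residual variance 0.68 gave 90.2% at n=58 and 99.5% at n=115.

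**5. Do other readings of the inputs give 115?** Using ρ1 alone, or 1-ρ1+ρ2, gives 59. A Bonferroni correction for 2, 3, 6 or 9 tests, which the section does not mention, gives 68, 74, 84 or 90. One reading does give 115: a difference between two pre-post change scores with all correlations equal to ρ has variance 4σ²(1-ρ), and 10.507×4×0.68/0.25 = 114.3. This reading is taken up under the objection.

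**6. The omitted class-by-lesson term.** A whole group shares each lesson, so the residual may contain a part common to the group in that lesson. Let ρ3 be that share of the total variance, taken out of the 0.68. The protocol gives no value, so ρ3 is an assumption here, shown over a range. With n students in k equal groups, in units of σ²:
Var = 2[(0.68-ρ3)/n + ρ3/k],
which equals (2/n)[(1-ρ1-ρ2)+(m-1)ρ3] with m=n/k.

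| Assumed ρ3 | Var, n=168, k=17 | Detectable d (90% power) | Power at d=0.50 |
|---|---|---|---|
| 0 | 0.00810 | 0.29 | 99.98% |
| 0.02 | 0.01021 | 0.33 | 99.9% |
| 0.05 | 0.01338 | 0.37 | 99.1% |
| 0.10 | 0.01867 | 0.44 | 95.5% |

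The same formula gives, at ρ3=0.05 and 0.10 respectively:
- first wave (74 students, 10 groups): 86% and 75% power;
- planned six classes (6×33×0.70, about 138 students): 87.6% and 69% power.

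**The case against.** **The arithmetic is not wrong.** This stands. The figure 115 is what the printed formulas give. The fault is that the design effect does not fit the base formula for the comparison described.

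**The factor 2 may reflect change scores.** The Main Outcomes section describes alertness and inhibition as changes, and both are measured at the start and end of each lesson. A difference of two pre-post changes with equal correlations reproduces 115 exactly. This stands in part: the authors may have meant it, and the article does not show the derivation. It does not rescue the text as written. Δ is defined on outcome levels, σ² is the overall outcome variance, the adjustment is attributed to students being their own controls, and situational engagement is measured only at the end of the lesson.

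**The error is conservative, and 58 is no safe replacement.** Both parts stand. On the stated inputs the need is overstated, and the 168 recruited exceed both figures. The 58 has no class-by-lesson term and no allowance for losses, although eight students dropped out.

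**The second wave.** A reader might infer that it was unnecessary because 74 students already give 95.8% power. The documents do not support that. It holds only at ρ3=0 and before losses; at an assumed ρ3 of 0.05 or 0.10 the first wave falls below 90%. The sentence on the second wave is also an accurate record of a decision taken against the 115 target.

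**Conclusion.** The point holds as a mismatch of formulas. For a within-student difference in outcome levels, the stated inputs imply 58 individuals for 90% power, and 115 corresponds to 99.6% power or a detectable d of 0.35. This rests on the protocol's own variance structure, with ρ1 and ρ2 as the only correlations.

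Two stronger readings should be resisted. The first is that 58 should have been the target: the missing class-by-lesson term works in the opposite direction, so 58 shows only what the inputs imply. The second is that the trial is compromised. Over the assumed ρ3 of 0 to 0.10, the 168 students in 17 groups detect d between 0.29 and 0.44, better than the planned 0.50. Those figures assume equal group sizes and no losses, whereas actual groups ranged from 1 to 18.

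Severity: should-fix. A sample size and power that recruitment relied on do not match, and the formula is to be reused, but no data or main analysis is affected.

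**What to change.** 1. Replace the multiplier by (1-ρ1-ρ2), or by (1-ρ1-ρ2)+(m-1)ρ3 with m the participating students per lesson (about 168/17=9.9) and ρ3 the lesson-level correlation. If the factor 2 was meant for a pre-post change-score contrast, say so and name the outcomes; it cannot apply to situational engagement.
2. Keep 115 as the historical prerecruitment target, with a note that it overstates the need on the stated inputs for a difference in levels, and that those inputs omit lesson-level correlation.
3. Add a small table of power and detectable effect for the achieved sample over an assumed ρ3 of 0 to 0.10.
4. Use the corrected formula for the forthcoming subgroup power approximations.
5. Leave the second-wave sentence as a record, qualified as resting on the 115 target.

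The cost is wording and one table. Data collection is complete and nothing in it changes. The correction should be made before the subgroup results are reported.

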### Student interviews (Part 3)

The evaluation of students’ experiences and perceptions of physically active academic lessons in a general upper secondary school will be conducted in the context of the cluster-randomized individual crossover trial described above. Of the 74 students recruited in the first wave of the trial, 59 consented (21 from mathematics lessons and 38 from foreign language lessons) to being invited for an interview (Figure 1). The aim is to interview as wide a range of students as possible; therefore, students will be selected in different ways. While one subject teacher proposed potential interviewees to the researcher, most students expressed their willingness to participate during their initial face-to-face contact with the researcher following the intervention. Thirty students were contacted and agreed to participate in the interviews in spring 2024. Ten students participated in the trial during mathematics lessons (5 taking the short syllabus and 5 the long syllabus), and 20 students during foreign language lessons (8 in English, 13 in Swedish, and 1 in German).

All 30 students were interviewed after participating in all three different lessons (treatments; see Figure 3). Ten students will be interviewed virtually via Microsoft Teams, and 20 students will be interviewed in person at their schools using an Olympus LS-PS-1 audio recorder. Semistructured interviews were chosen as a method to enable open and spontaneous responses and to capture the essence of students’ experience [83]. The questions are organized around the main themes (see Student interviews in the Supplemental material in Multimedia Appendix 1). The duration of the interviews will range from 37 to 70 minutes. The student responses will be transcribed and analyzed by using the engagement framework [23] and thematic analysis [56]. Thematic analysis is suitable for identifying patterns within and across data in relation to participants’ lived experience, views, and perspectives when the study aims to understand what participants think, feel, and do. Both deductive (literature-driven dimensions) and inductive (emerging from participants’ data) approaches will be used. The main focus of using the situational engagement framework is to analyze students’ responses to PAL. In addition, responses to PA breaks allow for a comparison of how PAL and PA breaks influence situational engagement.

## Results

Data collection has been completed. Fourteen teachers participated in the interviews (Part 1), 168 students participated in a cluster-randomized individual crossover trial in mathematics and foreign language lessons (Part 2), and 30 students participated in post-trial interviews (Part 3). The participating students received personalized feedback on their PA, physiological recovery, stress, and sleep measurements. In addition, teachers who conducted the intervention lessons received school-specific summaries, including information on students’ levels of PA, sleep patterns, and engagement during lessons. The results of the study will be reported in separate manuscripts, and the first findings based on the data analysis are expected by spring 2026. The results will be disseminated through plain-language summaries tailored for teachers and schools, published reports in the trial registry, and presentations at scientific and national seminars aimed at researchers and practitioners.

## Discussion

### Principal Results

This multidisciplinary mixed methods study aims to evaluate the experiences and perceptions of both teachers and students during physically active academic lessons in a general upper secondary school. The research interest is especially in facilitators, barriers, usefulness, and meaning of physically active academic lessons for the situational learning process. Additionally, the purpose is to examine the immediate effects of PAL and PA breaks on cognitive prerequisites for learning such as alertness and executive functions, and situational engagement, including behavioral, emotional, and cognitive engagement, as well as disaffection, competence experiences, and help-seeking among secondary school students. The study also aims to explore factors that modify these effects, such as physical and mental load, as well as perceived physical and academic competence. Aligning with previous findings, we hypothesize that this study will confirm the benefits [26-29], feasibility, and usability [41,43,50,51] of physically active classroom practices in general upper secondary education. Moreover, we expect the study to provide new insights into the role of PAL and PA breaks in situational learning processes in authentic educational settings, considering both teacher and student perspectives as well as potential moderating factors.

### Comparison With Prior Work

This is one of the first studies to explore experiences related to teaching, learning processes, and optimal instructions during physically active academic lessons in general upper secondary schools, while also examining the immediate effects of PAL and PA breaks on situational engagement and cognitive prerequisites for learning. Furthermore, the strength of this study lies in its combination of solid knowledge in both teaching and PA, allowing it to examine the phenomenon from both the student’s and the subject teacher’s perspectives at different levels of action (collected experiences and measured prerequisites for learning). A further strength of the study is that PA was measured from the thigh, enabling the distinction between sitting and standing during lessons. Additionally, HRV was monitored online to assess the balance between stress and recovery during classroom activities, which adds a novel dimension to the research.

### Implications and Future Research

The study’s findings will offer crucial, evidence-based insights into active classroom practices, aiding subject teachers and teacher education programs. This support helps teachers and schools adopt effective and innovative instructional strategies, pedagogical models, and designs, ultimately enhancing student learning and well-being in upper secondary education. Future research should study the phenomenon in other educational settings for older students, such as vocational secondary education and higher education, and across different cultural contexts. Research on the acute effects and students’ experiences should be extended to other subjects beyond mathematics and languages.

### Limitations

The study has faced certain limitations. The participation rate in the study was lower than desired, and possibly, less active or academically weaker students did not participate in the study, which may weaken the generalizability of the study results. The generalizability of teachers’ experiences is limited, as the findings are based on fourteen interviews from one municipality. While the interviews offer varied insights into integrating PA into different subjects, the experiences of individual subjects often rely on just one or two teachers. The teachers who participated were interested in the topic, but the views of less interested teachers were not captured. However, a couple of teachers who withdrew from the development project were also interviewed, which helps to understand why implementing PAL and PA breaks can be challenging.

### Conclusions

This study aims to address a gap in the literature by evaluating the feasibility and effectiveness of integrating physically active methods into academic lessons in upper secondary schools. Using a mixed-methods cluster-randomized individual crossover trial, the study seeks to enhance students’ learning and well-being.
